### Eligibility criteria

#### Inclusion criteria

Participants that meet the following criteria will be included in the study: (1) clinically diagnosed with Parkinson’s disease [21]; (2) brain computed tomography (CT) and other related imaging scans confirm no brain organic disease; (3) can stand for at least 30 min, with or without auxiliary equipment, and can walk independently for 3 m or more; (4) aged between 40 and 70 years; (5) clinically manifest frozen gait, with stage 2 or 3 Hoehn and Yahr; (6) respond to levodopa or other dopaminergic therapies; (7) exhibit stable condition, clear consciousness, no aphasia, and mental retardation and can understand the content of the scale and cooperate with the examination and treatment; and (8) agree to sign an informed consent form.

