### Exclusion criteria

Participants who meet the following will be excluded from the study: (1) secondary Parkinson’s disease; (2) those with deafness, aphasia, or severe cognitive impairment with difficulty to communicate normally; (3) patients with vascular dementia and frontotemporal dementia; (4) those with intolerance to standard treatment; (5) those who do not cooperate with the study program for rehabilitation; (6) those who have participated in other clinical trials within the past 3 months or are receiving other related treatments midway through the study, which may affect efficacy of this study; and (7) those with a history of neurological deficits other than Parkinson’s disease.

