### Criteria for discontinuing or modifying allocated interventions

There are no special criteria for discontinuing or modifying allocated interventions.

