### Recruitment and consent

Recruitment of patients began on June 1, 2020, and will be completed on December 31, 2021, or after the required number is obtained, whichever comes first. If there are not enough participants recruited by the deadline, we will submit an application for extension of time. Participant recruitment will consist of three strategies. Firstly, advertisements will be published on Shanghai Second rehabilitation hospital’s website or other online channels. Secondly, information will be shared via posters displayed in Shanghai Second rehabilitation hospital. Thirdly, recruitment posters will be distributed in nearby communities or primary clinics. Rehabilitation physicians will be requested to provide a list of individuals who meet the aforementioned inclusion criteria, while ineligible ones will be excluded. The study coordinator will invite eligible patients for the trial, by phone. Within 2 weeks of receiving the invitation, patients will receive a telephone call from a research assistant who will provide further information and ask them whether they are interested to participate. Finally, participants who provide a written informed consent and complete the baseline assessment will be randomized into the three groups and subjected to treatments.

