### Methods to handle protocol non-adherence and missing data

Analyses will be performed according to the intention-to-treat principle.

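### Exclusion criterion 6 removes patients for an event that can only occur after randomisation, and criterion 5 can be applied the same way; both conflict with the stated intention-to-treat analysis.

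*Protocol article*

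**What the plan says.** All references are to the protocol article.

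- **Exclusion criteria**, opening: "Participants who meet the following will be excluded from the study". Item 5 lists "those who do not cooperate with the study program for rehabilitation". Item 6 has two limbs. The first is "those who have participated in other clinical trials within the past 3 months"; the second is those who "are receiving other related treatments midway through the study, which may affect efficacy of this study".
- **Inclusion criteria**, item 7, already requires that patients "can understand the content of the scale and cooperate with the examination and treatment".
- **Recruitment and consent** fixes the order of events: "participants who provide a written informed consent and complete the baseline assessment will be randomized into the three groups and subjected to treatments".
- **Methods to handle protocol non-adherence and missing data** has a single provision: "Analyses will be performed according to the intention-to-treat principle". The Data analysis section names the same principle.
- **Criteria for discontinuing or modifying allocated interventions**: "There are no special criteria for discontinuing or modifying allocated interventions". The section on concomitant care makes no provisions.
- **Plans for assessment and collection of outcomes** names two recording times, baseline and 4 weeks. Trial design also mentions 3 months of follow-up.

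**The concern.** An eligibility criterion should be settled before allocation. If a patient can meet it only afterwards, it becomes a rule for removing randomised patients because of what they do during treatment. Patients who take up other treatment or stop cooperating may well differ in outcome from those who stay. Once they are removed, the arms compared are no longer the arms that randomisation produced.

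The intention-to-treat label does not repair this. It decides how available data are assigned to arms and cannot supply a 4-week gait or UPDRS measurement that was never taken because the patient had been excluded. Recruitment was under way when the article was written (Trial status), so assessments lost in this way cannot be recovered later.

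The removal may also differ by arm. Only the outcome assessor and the data analyst are blinded (Blinding). Participants are told their arm (Concealment mechanism), and the Discussion concedes that blinding therapists and patients is the hardest part of the design. A decision that someone is not cooperating, or has had other treatment, can therefore be made with the arm known.

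**Working it through.** **Step 1. When can each criterion be met?** The order is consent, baseline assessment, randomisation, treatment.

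| Item | Earliest time it can be met | Status |
|---|---|---|
| 6, first limb (other trial in past 3 months) | Screening | Proper baseline criterion |
| 6, second limb (other related treatment part-way through) | After randomisation | Post-randomisation exclusion |
| 5 (non-cooperation with the programme) | Screening or after randomisation | Ambiguous |

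Item 5 refers to the study's own programme, and ability to cooperate is already inclusion item 7. Both point towards conduct during treatment, but neither settles it.

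**Step 2. Can the sections be followed together?** Take a randomised patient who starts another related treatment in week 2. Exclusion criteria says the patient leaves the study. The discontinuation section has no criterion for stopping, and the concomitant-care section has no rule on other treatment. The non-adherence section says intention-to-treat, so the patient is analysed in the allocated arm. Staff cannot exclude this patient and also obtain the 4-week outcome that the analysis needs.

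**Step 3. How large could the effect be?** The plan has no figure for this, so what follows is an illustration.

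*From the plan (Sample size; Concealment mechanism):* 81 patients at 1:1:1, so 81/3 = 27 per arm. The UPDRS III reductions are 20.7 ± 16.6 (music), 7.9 ± 6.3 (exercise) and 2.6 ± 2.2 (control). The plan's 66 is reproduced by a one-way ANOVA with common SD 16.6: 22 per arm, power 91.2%. The present point does not depend on it.

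*Assumed:* no true effect; normal outcomes; the k patients with the lowest cooperation score are removed, with k = 3 (3/27 = 11%) or k = 5 (5/27 = 19%); the score correlates ρ with outcome; Welch t test at two-sided 5%.

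*Formula:* after the k lowest of 27 standard normal scores are removed, the remaining scores have mean m, with m = 0.203 for k = 3 and 0.316 for k = 5. The mean outcome in that arm shifts by ρ × m × SD.

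*Removal from one arm only, equal SDs:*

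| k | ρ | Shift (SD units) | Simulated 5% error |
|---|---|---|---|
| 3 | 0.5 | 0.5 × 0.203 = 0.10 | 7% |
| 3 | 0.8 | 0.8 × 0.203 = 0.16 | 10% |
| 5 | 0.5 | 0.5 × 0.316 = 0.16 | 9% |
| 5 | 0.8 | 0.8 × 0.316 = 0.25 | 16% |

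With nobody removed the simulated error is 5%, as it should be. At ρ = 0.3 it is about 6%.

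*Equal removal from both arms, equal SDs:* the two shifts cancel, so there is no bias in the difference. The error is about 6% at ρ = 0.5 and about 7% to 7.5% at ρ = 0.8.

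*Five removed from each arm, SDs 16.6 and 6.3:* the shifts do not cancel, because each scales with its own SD.

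- ρ = 0.5: 0.5 × 0.316 × (16.6 − 6.3) = 1.6 points; error 8%.
- ρ = 0.8: 0.8 × 0.316 × (16.6 − 6.3) = 2.6 points; error 14%.

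The planned music-minus-exercise difference is 20.7 − 7.9 = 12.8 points, so 1.6 to 2.6 points is about an eighth to a fifth of it.

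**The case against.** The case for leaving the text alone has four parts.

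**Criterion 5 may be a screening judgement.** It stands in the eligibility section, ineligible people are screened out before invitation, and the patients are inpatients on a rehabilitation ward whose cooperation can be observed. Overlap with inclusion item 7 proves little, since aphasia also appears in both lists. This stands: criterion 5 is ambiguous and not shown to act after randomisation. It still needs a time point, because staff could apply it either way.

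**The text excludes patients from the study and does not mention the analysis.** A reader might infer that the plan deletes randomised patients from the analysis. The article does not say that, and the non-adherence section points the other way. But exclusion from the study can still cost the 4-week outcome, which no analysis rule restores.

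**The direction of bias is open.** A reader might infer that the rule must favour music exercise, because only the exercise arms have an added programme to refuse. The documents do not support this. Controls have rehabilitation on the same schedule (5 times a week, 4 weeks, 1 h) and can fail to cooperate too. Patients who know they receive no added therapy might seek other treatment as often or more, and removing poorly performing controls would bias against music exercise. This objection stands in full.

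**One-sided removal is an extreme case.** It is least apt for music versus exercise, where both arms carry the added programme. Applying one-arm removal to SDs of 16.6 and 6.3 gives errors up to 25%, but that should not be read as the expected size. With five removed from each arm it falls to 8% to 14%. UPDRS III is also only a stand-in used for the sample size; the primary outcome is gait.

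**Conclusion.** The concern holds in a limited form. The second limb of criterion 6 is a stated exclusion after randomisation. It contradicts the intention-to-treat principle and does not fit the sections on discontinuation and concomitant care. Criterion 5 is ambiguous and can be used in the same way. This is a conflict within the article's own wording, so a fuller analysis plan would not remove it while the criterion stands.

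Bias is a risk here and has not been demonstrated. Its direction and size depend on how many patients are removed from each arm and how removal relates to outcome, and the documents give neither. Under the assumptions shown, it ranges from none (equal removal, equal SDs) to about 0.25 SD with an error near 16% (five removed from one arm only, correlation 0.8, equal SDs). The textual conflict does not rest on any of these assumptions.

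**What to change.** 1. In Exclusion criteria, delete the second limb of item 6, or limit it to other related treatment being received at screening. Leave the 3-month limb as it is.
2. State that item 5 is judged before randomisation.
3. Reconcile Exclusion criteria with the sections on discontinuation, concomitant care and non-adherence, so that all four give the same answer for a randomised patient.
4. Record later non-cooperation or other treatment as protocol deviations, and still make the 4-week assessment where the patient consents.
5. Analyse every randomised patient in the allocated arm. If anyone has already been removed under these criteria, include them; the article documents no such removal. An analysis without deviators may be shown only as a labelled sensitivity analysis.

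The cost is a wording amendment with ethical review. It needs no extra patients and no change to the sample size. The estimated effect may be slightly diluted, because patients who did not follow the programme stay in.

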### Additional consent provisions for collection and use of participant data and biological specimens

Not applicable.

## Intervention

### Explanation for the choice of comparators

We hypothesize that music exercise therapy can improve the frozen gait and motor function of patients with PD.

### Intervention description

The interventions in the three groups will be as follows.

### Music exercise therapy group

In addition to routine rehabilitation treatment, we will provide music exercise therapy, in which patients will perform scheduled exercises according to the rhythm of music. This will be performed 5 times a week for 4 weeks, with 1 h each time.

#### Music selection

Music therapists will screen musical tracks and rhythms according to the actual situation and music preferences of patients with Parkinson’s disease. Thereafter, the therapists will create a personalized music playlist for each subject, because the lyrics in the music may distract attention of the PD patients, hence selection of music with lyrics will be avoided. Each playlist will be loaded into a personal music player, and subjects are allowed to choose earplugs or headphones for maximum comfort. The mode setting of the music player will be “sequential play”, and not “random play.” Moreover, music will be played by a designated music therapist, and subjects will be also told that they can request changes to their playlists at any stage during intervention.

#### Exercise therapy

While listening to music using earphones, the patients will be subjected to conduct flat start walking, turn around, and stop (at the end) trainings, as well as narrow space walking and stair step training according to the beat in the music. The patients will be expected to simultaneously complete a cycle of exercise relative to completion of the music playlist.

#### Points for attention

A precondition of the exercise therapy will be to ensure patient safety. Therefore, we will set various safety requirements with regard to the venue, patients’ clothing, and accompanying personnel, among others. Particularly, care will be taken to ensure that the site is spacious, bright, and free of obstacles, and the ground shall is flat, antiskid, and dry. Clothes and shoes will be checked to ensure that patients feel soft and comfortable during training, which is convenient for cooling and avoiding unnecessary body injury. In addition, patients will be expected to be accompanied and guarded by their families during training. Appropriate warm-up, including relatively slow and gentle exercises, will be conducted prior to the training to increase activity across all parts of the body, as well as enhance posture coordination and breathing, thereby prevent muscle straining.

### Exercise therapy group

Apart from routine rehabilitation treatment, patients in this group will be subjected to exercise therapy without music. Patients will be allowed to wear earphones without music, then subjected to flat start walking, turn around, and stop (at the end) training, as well as narrow space walking and stair step training, 5 times a week for 4 weeks, with 1 h each time.

### Control group

Participants in this group will be subjected to routine rehabilitation treatment, comprising the following: (1) routine drug treatment; (2) joint mobilization technology; (3) posture correction training; (4) balance training; (5) limb passive and active activity training; (6) walking training; (7) physical factor treatment; (8) operation ability training; and (9) daily life ability training. These will be performed 5 times a week for 4 weeks, with 1 h each time.

### Criteria for discontinuing or modifying allocated interventions

There are no special criteria for discontinuing or modifying allocated interventions.

### Strategies for improving adherence to interventions

We will adopt a variety of strategies to improve adherence to interventions. For example, we hope to establish a good relationship with the participants and fully simplify the intervention program to win their trust and cooperation. In addition, we will strengthen guidance to the participants and strive to understand and solve their problems in time to eliminate any concerns.

### Relevant concomitant care permitted or prohibited during the trial

No special provisions.

### Provisions for post-trial care

Not applicable.

### Outcome measures

Therapeutic evaluation will be carried out by the same team member who will be blinded to treatment allocation. The primary evaluation index of this study will be change of gait in PD patients, whereas the secondary evaluation indices will include evaluation of limb function, activity of daily life, and fall risk. We will adopt a three-dimensional gait analysis system for evaluation of gait information and surface electromyography for muscles related to lower limbs. We will employ the Unified Parkinson’s Disease Rating Scale (UPDRS) to assess the mental cognition, motor function, and daily living ability [22], while the Fall Efficacy Scale (FES) will be used to assess the risk of falls. Data across all measurements will be recorded in the data center [23].

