**Methods/design:**

This three-arm randomized controlled trial will evaluate clinical efficacy of music exercise therapy in improving the freezing of gait in Parkinson’s patients. We will recruit a total of 81 inpatients with Parkinson’s disease, who meet the trial criteria. The patients will randomly receive music exercise with and without music as well as routine rehabilitation therapies, followed by analysis of changes in their gait and limb motor function after 4 weeks of intervention. We will first use a three-dimensional gait analysis system to evaluate changes in patients’ gait, followed by assessment of their limb function, activity of daily living and fall risk.

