### Concealment mechanism

After signing the informed consent, participants will be randomly divided into the three aforementioned groups, at a ratio of 1:1:1. We will keep the allocation hidden during randomization. Slips of paper with treatment allocation will be placed in a sequentially numbered sealed opaque envelope and then opened in turn after obtaining informed consent. The research assistant will inform participants of their assigned study arm.

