### Blinding

The outcome assessor and data analyst will be blinded to the treatment allocation. Specifically, the assessor will enter data into a Microsoft Excel sheet, after completion of data collection, without knowledge of treatment group assignments. All entered data will be assigned corresponding codes and cleared of unnecessary information. Blinding will be broken after the data has been analyzed.

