### Adverse event (AE) reporting and harms

Any adverse medical events to the participants will be collected after the subjects have signed the informed consent and agreed to participate in the study. Events will not be considered to be related to music exercise therapy if they occur after the participant has signed the informed consent, but before the intervention. All adverse events occurring after enrolment into the study and before discharge will be recorded and reported to the local Institutional Review Board.

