## Discussion

FOG, the most common gait abnormality that occurs during mid and late stages of Parkinson’s disease, can lead to falls and injuries. To date, drug treatment has not effectively managed the disease although rehabilitation treatment has shown significant promise. Early recognition and intervention of FOG can reduce disability rate and improve prognosis. Results from our pilot study showed that music exercise therapy can improve the FOG of Parkinson’s patients and improve their quality of life. However, its long-term effects are not known, necessitating further research. Therefore, we propose a prospective randomized clinical trial to validate the clinical efficacy of music exercise therapy for treatment of FOG in Parkinson’s patients.

To eliminate the interference of headphone wearing behavior on test results, we have proposed a set of exercises without music. Bias exists in all clinical trials. Therefore, we acknowledge that blinding music therapists and patients to the intervention will be the most challenging aspect during designing of this randomized controlled trial. Consequently, we will blind our evaluators to minimize potential bias and further adopt a three-dimensional gait analysis as part of the approach for evaluating our results. Previous studies have widely used this analysis system to evaluate gait, especially in neurological diseases. We will also apply time and space and ankle kinematic parameters as well as electrophysiological measurements during the process of walking, and this is expected to provide quantitative information about gait and reduce the interference of subjective factors in the scale evaluation. We believe that our findings will help improve FOG and motor function in patients with Parkinson’s disease.

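### The secondary outcome called fall risk is measured only by the Fall Efficacy Scale, which rates perceived confidence about falling among participants who know their arm, so a gain should not be read as lower fall risk

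*Protocol article*

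**What the plan says.** Under Outcome measures the primary index is change of gait, and "the secondary evaluation indices will include evaluation of limb function, activity of daily life, and fall risk". The same section assigns the instrument: "the Fall Efficacy Scale (FES) will be used to assess the risk of falls". The abstract (Methods/design) uses the same label for what follows the gait analysis: "followed by assessment of their limb function, activity of daily living and fall risk". Neither place names a fall count, a fall diary or any other fall measure as an outcome.

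On blinding, Outcome measures says that one team member, blinded to allocation, carries out the therapeutic evaluation. The Blinding section says: "The outcome assessor and data analyst will be blinded to the treatment allocation". Under Concealment mechanism, "The research assistant will inform participants of their assigned study arm". The Discussion concedes that "blinding music therapists and patients to the intervention will be the most challenging aspect" and gives the response: "we will blind our evaluators to minimize potential bias". Plans for assessment and collection of outcomes names gait analysis and UPDRS for the evaluator who does not know the group; it does not name the FES.

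On harms, "All adverse events occurring after enrolment into the study and before discharge will be recorded". Falls are not mentioned there.

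**The concern.** Perceived confidence and the risk of falling are different quantities and can move apart. The two exercise arms practise turning, narrow-space walking and stair steps. A patient who has done so may feel surer and move about more without falling less often. The protocol fixes both the instrument and its interpretation, so an analyst who follows the text would report an FES gain as a reduction in fall risk.

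Knowledge of the arm adds to this. A confidence rating is open to expectation, and the safeguard on which the protocol relies is a blinded evaluator. That protects measurements the evaluator makes. It does not protect an answer the participant gives.

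At stake is the meaning of one of three secondary domains. The subject is not marginal for this trial: the abstract, the background and the discussion all present freezing of gait as a cause of falls, so readers will take a result labelled fall risk seriously.

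**Working it through.** The point turns on what is measured and who knows the allocation, so the protocol has no figure to reproduce. The check sets its sections side by side; one illustrative calculation follows.

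**1. Label against instrument.** Outcome measures and the abstract name the outcome fall risk. The only instrument assigned to it is a scale of fall efficacy. The mismatch can be read from the protocol's own words, without the cited source for the scale.

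**2. Who knows the arm.**
- Assessor and analyst: blinded (Blinding).
- Participants: told their arm (Concealment mechanism). The Discussion calls blinding them the most challenging aspect and relies on blinded evaluators.
- Who answers the FES: not stated. That it is answered by the patient is a standard property of such a scale and is taken here as an assumption.

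**3. Fit with the protocol's rationale.** Background and rationale criticises earlier music-therapy studies for relying on subjective scale scores, and the Discussion offers gait analysis as the remedy. That remedy covers gait. It does not reach the fall outcome, which still rests on a scale score alone.

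**4. How large could an expectation effect be?** Inputs:
- Evaluable patients per arm: 66/3 = 22 (Sample size); with no dropout, 81/3 = 27.
- Two-sided α = 0.05 (Sample size).
- Expectation effect on the FES, d = 0.3 to 0.5 SD: an assumption, since the documents give none.

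Method: two-sample t test between two arms, degrees of freedom 2n − 2, noncentrality d × √(n/2), no true change in falls.

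| n per arm | d | noncentrality | chance of p < 0.05 |
|---|---|---|---|
| 22 | 0.3 | 0.3 × √11 = 0.99 | 0.16 |
| 22 | 0.5 | 0.5 × √11 = 1.66 | 0.37 |
| 27 | 0.3 | 0.3 × √13.5 = 1.10 | 0.19 |
| 27 | 0.5 | 0.5 × √13.5 = 1.84 | 0.44 |

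These compare with a nominal 0.05. Under the assumption, an expectation effect alone would produce a significant pairwise FES difference well above the nominal rate, but in fewer than half of trials.

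**5. Is there direct information on falls?** The adverse-event section covers events from enrolment to discharge. It neither names falls nor sets an observation window common to the arms. A fall without injury may not be recorded, and time to discharge may differ between patients. Whether usable counts exist cannot be settled from the document.

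**The case against.** - **Self-completion is not stated.** No section says who answers the FES or describes its items. This stands. The mismatch of label and instrument does not depend on it; the blinding part does and is therefore worded conditionally.
- **The protocol does not claim blind participants.** It claims a blinded assessor and analyst, concedes the difficulty with patients, and names only gait analysis and UPDRS for the blinded evaluator. This also stands. A reader might infer that the protocol presents the FES as a blinded measurement, or misstates its blinding. The text does not support that: the general sentence in Outcome measures says who carries out the evaluation, not that the ratings are blind.
- **No fall-reduction claim is announced.** The trial objectives cover freezing of gait, motor function and quality of life. A reader might infer that the trial is set to claim a safety benefit. Nothing in the document says so. What it does is fix a label that would make an FES gain read as reduced risk.
- **The bias would usually miss significance.** Correct under the assumed 0.3 to 0.5 SD. Expectation could produce a false fall-risk finding; it cannot be said that it would.
- **Adverse-event records are no ready substitute.** Also correct, for the reasons in step 5 of the working. Falls over 4 weeks in about 27 supervised patients per arm are likely to be few.

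A concern about the construct survives these points. A charge of misreported blinding does not.

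**Conclusion.** The concern holds in a limited form. The protocol labels a secondary outcome fall risk and fixes as its only measure a scale that, by its name, rates perceived confidence about falling. Because participants know their arm, a gain could reflect expectation, and it should not be read as reduced fall risk.

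The size is modest: one of three secondary domains. The primary gait outcome, the sample size and the randomisation are unaffected. The 16% to 37% figure at 22 per arm rests wholly on the assumed 0.3 to 0.5 SD effect and illustrates scale only. The blinding part rests on participants supplying the FES answers. The FES remains a legitimate outcome for what it measures; its label and interpretation need changing.

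**What to change.** 1. In the abstract and under Outcome measures, rename the outcome *fall-related self-efficacy (FES; participants not blinded)*, and drop risk of falls as its interpretation.
2. State that no conclusion about fall risk will be drawn from the FES alone.
3. Say who completes the FES and, if participants supply the answers, note that assessor blinding does not protect this rating.
4. Confirm whether falls, including those without injury, are recorded alike in all arms. If they are, tabulate by arm the number of patients with at least one fall and the total number of falls over the 4-week period, as a descriptive check and not a test. If they are not, omit the table and make no statement about falls.

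Items 1 to 3 are wording changes. Item 4 costs one table if the records are adequate; if they are not, adding fall recording would be extra work that this point does not require. The trial gives up a stronger-sounding claim for one secondary outcome. Visits, interventions and sample size do not change.
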